## 2. Materials and Methods

### 2.1. Study Design and Setting

This is a single-blind, monocenter, randomized trial, with serial baseline–intervention–follow-up periods and three parallel intervention arms (see Figure 1). The total study duration per participant is 16 weeks and it will be conducted at Amsterdam UMC. All participants will perform two baseline assessments four weeks apart (i.e., baseline period), followed by an eight-week intervention period and a post intervention assessment. Subsequently, after 4 weeks a follow-up assessment will be conducted. This will allow the evaluation of baseline stability, the evaluation of the short-term durability of treatment effects, and enhanced statistical power by enabling within-subject modeling.

Eligibility criteria will be assessed during intake assessment prior to enrollment. The participants will be randomly allocated to one of the three intervention arms: (1). HIIT; (2). CAT; (3). MA. Stratified block randomization via CASTOR EDC will be used to minimize selection bias. Randomization will be stratified by disease diagnosis (PD or MS), with six blocks of four participants per diagnosis group allocated sequentially over the course of this study.

This study is approved by the medical ethical review board of the Amsterdam UMC (2021.0476). The current study status: enrollment and data collection. Additionally, blood samples will be collected and stored in the HersenFIT study biobank for future biomarker analyses, as approved by the institutional biobank review committee.

This study was prospectively registered at www.ClinicalTrials.gov (ID: NCT05357638).

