#### 2.2.1. Safety Monitoring and Withdrawal

Safety procedures will follow the protocol approved by the accredited medical ethical review board. All adverse events are recorded and graded according to the Common Terminology Criteria for Adverse Events. Serious adverse events will be reported within 7 days to the accredited medical ethical review board.

All exercise sessions will be supervised by qualified physiotherapists experienced in managing Parkinson’s disease and multiple sclerosis, ensuring the appropriate handling of disease-specific risks during training.

Participation is voluntary. The participants may withdraw at any time. Those who withdraw before completing the second baseline assessment will be replaced; those who withdraw from the intervention phase will be invited to complete the post intervention and follow-up assessments.

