#### 2.2.2. Sample Size

The sample size was calculated based on the primary outcome (HADS total score). Anticipated improvements were 6 points in the HIIT group and 3 points in the CAT group, with an standard deviation (SD) of 6 [64]. Using G*Power (version 3.1) for repeated measures analysis of variance with an alpha of 0.05 and 80% power, a total of 42 participants is required. Accounting for an expected 15% dropout rate, 48 participants will be recruited.

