### 2.5. Statistical Analysis

Statistical analyses will be conducted using R or Stata, with the significance set at *p* < 0.05 (two-tailed). The primary analysis will follow the intention-to-treat principle and per protocol analysis will be performed as a sensitivity analysis.

Continuous variables will be presented as mean (SD) or median [IQR] values based on normality. Categorical variables will be reported as frequency (%). Normality will be assessed using histograms and Q-Q plots. In case normality assumptions are violated, a log-transformation will be explored.

Baseline characteristics, including age, sex, disease severity, anxiety, depression, and medication use, will be presented for each intervention arm and for each disease type (PD, MS) using descriptive statistics.

Linear mixed models (LMMs) will be used to analyze the longitudinal changes in anxiety and depression across time points (baseline, intervention, and follow-up) and between intervention arms (HIIT, CAT, and MA). These factors will be added to the model as fixed factors. All outcomes will serve as dependent variables in separate models. Participant ID will be added to the model as a random effect to account for intra-individual correlations. Age, sex, medication, and mobility severity (i.e., TUG) will be added to the model as covariates and interaction effects for disease will be investigated. Exploratory subgroup analyses will be conducted if the interaction term is significant. The MA group will be the reference group.

The analyses of secondary outcomes will be exploratory in nature. No formal adjustment for multiple comparisons will be applied; exact *p*-values will be reported, and the results will be interpreted cautiously considering the increased risk of Type I error.

For all primary and secondary outcomes, estimated effects with 95% confidence intervals will be reported from the LMM, alongside standardized effect sizes (Hedges’ g with 95% confidence interval) to facilitate clinical interpretation.

Missing data will be expected, but LMMs are generally robust to missing data. Outliers will be identified using residual diagnostics and sensitivity analyses will be performed with and without outliers to evaluate robustness.

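### The dropout allowance in section 2.2.2 is miscalculated: 48 recruits retain the required 42 only up to 12.5% dropout, not the expected 15% (minor)

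*Protocol article*

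**What the plan says.** Section 2.2.2 (Sample Size) of the protocol article gives the sizing in three steps.

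- The assumptions: "Anticipated improvements were 6 points in the HIIT group and 3 points in the CAT group, with an standard deviation (SD) of 6".
- The method and its result: "Using G*Power (version 3.1) for repeated measures analysis of variance with an alpha of 0.05 and 80% power", from which "a total of 42 participants is required".
- The allowance for loss: "Accounting for an expected 15% dropout rate, 48 participants will be recruited".

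Section 2.2.1 (Safety Monitoring and Withdrawal) bears on what counts as a loss. On early withdrawals it says "Those who withdraw before completing the second baseline assessment will be replaced". On later ones it says "those who withdraw from the intervention phase will be invited to complete the post intervention and follow-up assessments". Section 2.5 plans an intention-to-treat primary analysis with linear mixed models.

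**The concern.** An allowance for dropout is meant to leave the required number after the expected loss. A dropout rate is normally read as a share of those who enter the trial, so the required number is divided by one minus the rate. Here 42, 15% and 48 do not satisfy that relation, although the sentence presents 48 as covering the expected loss.

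What is at stake is the accuracy of the justification for the sample size. The printed 80% power belongs to 42 participants, and a reader will take it that 42 are still expected at the end if dropout runs at the planned rate. On the printed figures the expected number is slightly lower. Whether 42 is itself the right requirement is a separate question and is not examined here.

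**Working it through.** **Inputs from section 2.2.2.** Required number 42; expected dropout 15%; recruited 48.

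**Step 1: reproduce the printed 48.** Adding 15% to the required number gives 42 × (1 + 0.15) = 48.3, which is 48 to the nearest whole number (49 if rounded up). The section states no inflation formula, so this is an inference about how 48 arose, but it fits the printed figure.

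**Step 2: the number that retains 42 after a 15% loss.** N = 42/(1 − 0.15) = 42/0.85 = 49.4, rounded up to 50. That is 2 more than printed.

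**Step 3: what 48 delivers.**
- Expected losses at 15%: 48 × 0.15 = 7.2.
- Expected to remain: 48 × 0.85 = 40.8, about 41, which is 42 − 40.8 = 1.2 short.
- Losses that 48 can absorb: 48 − 42 = 6, a rate of 6/48 = 12.5%.

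**Step 4: size in terms of power.** Section 2.2.2 does not give the effect size f, the number of measurements, the correlation between them or the type of repeated-measures test, so the following rests on assumptions. The anticipated difference is 6 − 3 = 3 points with an SD of 6, so d = 3/6 = 0.5, and for two groups f = d/2 = 0.25. Assume the within-between interaction test with f = 0.25, 3 groups, m = 2 measurements, correlation ρ = 0.5, no sphericity correction and alpha 0.05. The noncentrality is λ = f² × N × m/(1 − ρ), with 2 and N − 3 degrees of freedom. At N = 42, λ = 0.0625 × 42 × 2/0.5 = 10.5. The smallest N that reaches 80% under these settings is exactly 42, which is why they were chosen.

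| Participants contributing | Power |
|---|---|
| 42 | 80.3% |
| 41 | 79.2% |
| 40.8 (expected at 15% loss of 48) | 79.0% |
| 40 | 78.1% |

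The expected shortfall therefore costs 80.3 − 79.0 = 1.3 percentage points, and power ends about 1 point below the nominal 80%.

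**Step 5: how far the other sections reduce the loss.** The shortfall of 1.2 arises only if all 7.2 expected losses are unreplaced and yield no usable outcome data. Under section 2.2.1, withdrawals before the second baseline assessment are replaced. If at least 1.2 of the 7.2 fell there, 42 would be retained. The same holds if at least 1.2 of those who stop the intervention still attend the later assessments.

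**The case against.** The strongest answer has three parts.

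First, 48 can be reproduced. Adding 15% to 42 is a common shortcut, and the gap from the standard result is 2 recruits. This explains the number but does not make the sentence right. The inputs are printed and the check is a single division, so there is no unknown software setting to excuse a difference. The reserve is 6 where 8 are needed (50 − 42).

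Second, loss of usable data may be well under 15%. Early withdrawals are replaced, those who stop the intervention are invited back for assessment, and a mixed model keeps participants with incomplete data. Anyone past the second baseline already has two HADS measurements (Table 1). This largely stands and makes 40.8 close to a worst case. It has limits: an invitation does not guarantee attendance, and two pre-intervention scores alone say little about the effect of the intervention. Also, section 2.2.2 sizes the trial by repeated-measures ANOVA with an explicit allowance for dropout, and on that logic the allowance should be computed correctly.

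Third, the power effect is trivial and rests on assumed settings. This also stands. A reader might infer from the arithmetic that the trial misses its required size and fails to reach 80% power on the plan's own figures. The document does not support that. It does not print the inputs needed to compute power, and its replacement and follow-up rules may close a gap of about one participant.

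**Conclusion.** The allowance is wrong as written, and the point is minor. That 48 covers at most 12.5% loss follows from the printed figures alone, if the 15% is read in the usual way as a share of those recruited. The shortfall at 15% is about one participant.

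The estimate of about one power point depends on the assumed G*Power settings in the working, and on dropouts contributing nothing to the analysis. It shows the order of size and is not a statement of the trial's actual power. The error does not show that the trial is underpowered, and it does not affect the design or the analysis. Section 2.2.2 also does not say which withdrawals the 15% covers, and no particular meaning is assumed here.

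**What to change.** Keep 48 and correct the last sentence of section 2.2.2. Suggested wording: 48 participants will be recruited, which retains the required 42 if dropout is at most 12.5%; at the expected 15% about 41 remain, and power is then marginally below 80% if dropouts contribute no data.

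If an exact power figure for 15% dropout is to be printed, the sponsor should recompute it with its own G*Power inputs. The percentages in the working come from assumed settings and should not be copied into the protocol.

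The cost is one sentence and a slightly less favourable statement of power. No extra enrolment is needed, the 24 per diagnosis stay as planned, and no procedure changes.

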### 2.3. Outcome Assessment

Baseline assessments will include demographic, disease-specific characteristics, and pharmacotherapy (participants will be asked to maintain their existing regimen unless medically required to adjust). The assessor will be blinded to group allocation. Outcome measures will be assessed at baseline, pre intervention (week 4), post intervention (week 12), and follow-up (week 16). An overview is provided in Table 1.

#### 2.3.1. Primary Outcome

The validated HADS will be used to assess symptoms of anxiety and depression [60]. This 14-item self-report tool includes two subscales (HADS-A and HADS-D) each scored from 0 to 21, with higher scores indicating greater severity. A total score (range 0–42) will also be calculated.

#### 2.3.2. Additional Outcomes: Non-Motor Symptoms

In addition to the HADS, affective disturbances will also be monitored using visual analog scales (VAS) [65]. The participants will rate the severity of depression and anxiety using a 100 mm VAS (1 = ‘extremely depressed/anxious’ and 10 = ‘cannot be happier/not anxious’) three times per week.

Cognition will be evaluated with the symbol digit modalities test (processing speed) [66], Stroop color–word test (executive function) [67], and trail making test (task switching) [68]. A VAS will be used to rate concentration.

Fatigue will be assessed with the checklist individual strength (CIS-20r) fatigue subscale. A score ≥35 is indicative of severe fatigue [69]. Sleep quality will be investigated using the insomnia severity index (ISI) [70]. A score of ≥10 is indicative of insomnia. VAS scales (1–10) will assess perceived fatigue and sleep three times per week.

#### 2.3.3. Additional Outcomes: Motor Symptoms

The 10 m walk test (10MWT) and timed up and go (TUG) test will be used to assess functional mobility [71,72]. During the 10MWT participants will be instructed to walk a 10 m marked course at comfortable walking speed and for the TUG test participants will be instructed to rise from the chair, walk 3 m, turn around, return to the chair, and sit down again. The average speed from three trials will be registered together with the average step number.

Dexterity will be assessed using the nine-hole peg test (9HPT) [73]. Participants are instructed to place and remove nine pegs from a pegboard as quickly as possible using the dominant hand and the non-dominant hand separately.

Specifically for participants with PD, prior to motor symptom assessment, time since last dose of levodopa and the participant’s ‘on/off’ medication state will be recorded; this is not applicable for people with MS.

#### 2.3.4. Additional Outcomes: Neuroplasticity and Neurodegeneration

Structural and functional MRI scans will be performed pre and post intervention (i.e., week 4 and week 9) on a Siemens (Erlangen Germany) Vida 3T equipped with a 64-channel head coil. T1-weighted magnetization-prepared rapid gradient echo (MPRAGE), fluid-attenuated inversion recovery (FLAIR), neuromelanin (NM), quantitative susceptibility mapping (QSM), diffusion-weighted imaging (DWI), and resting state functional MRI sequences will be employed to examine brain volumetrics, white matter lesions, the quantification of neuromelanin in the substantia nigra, iron deposits, whiter matter integrity, and resting state functional connectivity, respectively. These measures are incorporated to better understand the potentially underlying neuroprotective mechanisms.

Weekly non-fasting plasma and serum samples (10 mL; aliquot of 0.5 mL) will be collected to measure the concentration of brain-derived neurotrophic factors (BDNFs) [74,75], a marker of neuroplasticity, and neurofilament light (NfL) [76], a marker for axonal damage. Aliquots will be stored at −80 °C until processing for biomarker analysis. BDNF will be measured in serum using the Quanterix Simoa kit; serum NfL with a validated in-house Simoa assay [77]. At first blood draw, additional plasma and serum will be collected for future analyses (10 mL; aliquot of 0.5 mL).

#### 2.3.5. Additional Outcomes

The Nottingham extended activities of daily living scale (NEADL), a self-reported outcome measure to assess instrumental activities of daily living, will be utilized to examine four participation domains: mobility, kitchen, domestic, and leisure activities [78]. The 22-item scale is scored from 0 to 3, with higher scores indicating greater functional independence.

Health-related quality of life will be assessed with the 36-item short-form health survey (SF-36) [79]. Scores are transformed to a 0–100 scale for the different subscales (e.g., physical functioning, mental health, and pain), with higher scores reflecting better perceived quality of life.

The 13-item physical activity scale for individuals with physical disabilities (PASIPD) was used to examine 7-day physical activity in daily life, assessed as the weekly amount of physical activity expressed in metabolic equivalent hours per day (METS) [80]. Changes in PASIPD scores can indicate a shift in habitual activity patterns.

To determine the appropriate training intensities of the HIIT and CAT interventions, a cardiopulmonary exercise test (CPET) will be performed. Peak oxygen uptake (in ml/min and ml/kg/min) and oxygen uptake at the first and second ventilatory threshold, as well as load (in Watt) and heart rate (in bpm), will be registered. The CPET is considered the gold-standard measure of aerobic capacity. To determine the intensity for the MA group, participants in this group will wear a Fitbit Inspire 2 watch. The average daily step count during the baseline period will form the basis of the step count in the intervention period. Daily step count will be monitored during the baseline and intervention period.

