Furthermore, exercise intensity appears to be an important driver of neuroplastic adaptations; however the optimal intensity remains unclear [40]. Emerging research suggests that exercise may contribute to slowing disease progression through neuroprotective mechanisms [28,29]. These include the preservation of regional brain volumes—particularly in the hippocampus and cortical areas [41,42]—the enhancement of white matter integrity (e.g., increased fractional anisotropy) [43], and the modulation of resting state functional connectivity [44]. One frequently studied mechanism is the upregulation of neurotrophic factors, such as brain-derived neurotrophic factor (BDNF), which supports synaptic plasticity, learning, and memory [45,46]. Notably, reduced BDNF concentrations have been associated with affective symptoms, including anxiety and depression [47]. Exercise, and especially high-intensity exercise, has been shown to increase BDNF expression, even in populations with neurodegenerative conditions, and this upregulation may mediate improvements in mood as well as broader neuroplastic changes [48,49,50]. This growing evidence base provides a strong rationale for evaluating exercise as a therapeutic strategy targeting both non-motor symptoms and neurobiological outcomes.

Despite the growing interest, comparative studies evaluating the effects of HIIT and CAT on non-motor symptoms and neuroplasticity in PD and MS remain scarce [51,52]. Moreover, people with these conditions may face barriers to engage in structured HIIT and CAT exercise interventions, such as limited accessibility, fatigue, or lack of time, which highlights the need for more flexible alternatives [53]. Movement advice (MA), which involves personalized guidance to increase daily physical activity, offers a pragmatic, home-based approach that may improve feasibility and adherence. We are optimistic that evaluating MA alongside CAT and HIIT will provide valuable insights into the feasibility, effectiveness, and individualization of exercise-based interventions for managing non-motor symptoms in PD and MS. This randomized controlled trial aims to investigate the effects of HIIT on non-motor symptoms, particularly anxiety and depression, compared with CAT and MA in individuals with PD and MS. Secondary objectives include evaluating the impact of exercise on blood and MRI measures of neuroplasticity, neurodegeneration, and overall quality of life.

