### 2.4. Intervention

All interventions will consist of an 8-week individually tailored exercise program based on each participants’ physical fitness level. This duration reflects a balance between effectiveness and feasibility [81]. Detailed descriptions of the interventions are provided in the supplementary Template for Intervention Description and Replication (TIDieR) checklist (Supplementary File S1).

HIIT and CAT will be performed twice weekly for 8 weeks on a cycle ergometer under the supervision of a physiotherapist. The HIIT consists of 5–6 45 s bouts of high-intensity bursts at 85–95% of peak load reached during a CPET, alternating with low-intensity 90 s bouts at an intensity below the first ventilatory threshold. CAT consists of two 20 min bouts at intensities below the first ventilatory threshold interspersed with 2 min breaks.

The participants in the MA group will receive information on physical activity based on the Dutch physical activity guidelines, which recommend engaging in at least 150 min of continuous moderate-to-vigorous-intensity physical activity per week and performing muscle-strengthening exercises on two days per week [82]. To support self-monitoring, each participant will be provided with a Fitbit smartwatch to track daily step counts throughout this study. The average daily step count recorded during the baseline phase will serve as the individualized reference point for their movement goals. During the eight-week intervention period, participants in the MA group will be encouraged to increase their daily step count by approximately 3000 steps on at least five days each week, relative to their personal baseline [83].

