* moment of outcome assessment; ^a^ only for people with Parkinson’s disease; ^b^ only for people with multiple sclerosis; ^c^ for participants that perform intervention at home, blood is collected and assessed in weeks 1, 4, 8, 12, and 16. Abbreviations: HADS, hospital anxiety and depression scale; VAS, visual analog scale; MoCA, Montreal Cognitive Assessment; SDMT, symbol digit modalities test; SCWT, Stroop color–word test; TMT, trial making test; CIS-20r, checklist individuals strength 20r; ISI, insomnia severity index; PDQ-8, Parkinson’s disease questionnaire 8-item; MSIS, multiple sclerosis impact scale; SF-36, short form 36-items; MDS-UPDRS, Movement Disorder Society—unified Parkinson’s disease rating scale; EDSS, expanded disability status scale; 10MWT, 10 m walking test; TUG, timed up and go test; NHPT, nine-hole peg test; PASIPD, physical activity scale for individuals with physical disabilities; NEADI, Nottingham extended activities of daily living index; BDNF, brain-derived neurotrophic factor; NfL, neurofilament light; MRI, magnetic resonance imaging; CPET, cardiopulmonary exercise test.

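### The time of randomisation is not stated, but arm-specific procedures in weeks 1–4 imply that it precedes the second baseline, so the week-4 HADS is probably post-allocation and the replacement rule is at odds with intention-to-treat

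*Protocol article*

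**What the plan says.** Section 2.1 places eligibility at intake, then describes random allocation to three arms stratified by diagnosis. Two baseline assessments four weeks apart precede the eight-week intervention. No sentence places allocation before or after either assessment. One stated purpose of the double baseline is to judge whether symptoms are stable before treatment.

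Two arm-related procedures fall inside that baseline period:

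- Step counting. Section 2.3.5: "To determine the intensity for the MA group, participants in this group will wear a Fitbit Inspire 2 watch". It continues: "The average daily step count during the baseline period will form the basis of the step count in the intervention period", and "Daily step count will be monitored during the baseline and intervention period". Section 2.4 repeats, in its MA paragraph, that the baseline count is the reference for the step goals and that the watch serves self-monitoring. The same paragraph says "each participant will be provided with a Fitbit smartwatch to track daily step counts throughout this study".
- Blood sampling. Section 2.3.4 and Table 1 have weekly draws throughout the baseline period. Footnote c makes an exception: "for participants that perform intervention at home, blood is collected and assessed in weeks 1, 4, 8, 12, and 16". MA is the arm the Introduction calls home-based (it "offers a pragmatic, home-based approach that may improve feasibility and adherence"), whereas section 2.4 has HIIT and CAT supervised by a physiotherapist.

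Section 2.3 blinds the assessor. Section 2.3.1 defines the primary outcome, the HADS, as self-reported. On withdrawal, section 2.2.1 says: "Those who withdraw before completing the second baseline assessment will be replaced". Section 2.5 says: "The primary analysis will follow the intention-to-treat principle", and makes MA the reference group.

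**The concern.** A baseline is useful in a randomised comparison because allocation cannot have influenced it. If MA participants are identified in time to wear a step counter in weeks 1–4, their week-4 HADS no longer has that property. They may score differently because they know they will receive advice only, or because watching their step count has already changed how much they walk. HIIT and CAT participants may react to their own allocation. Since the HADS is self-reported, blinding the assessor does not protect against this.

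Three things are at stake. The baseline-stability check would mix natural variation with reactions to allocation. The HIIT–MA and CAT–MA estimates could be biased, both of them together, because MA is the reference. And people who leave between allocation and week 4, possibly because of their arm, would be replaced although the analysis is described as intention-to-treat.

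**Working it through.** **1. The plan's own sample-size figures, for reference.** The 42 required reproduces with d = 3/6 = 0.5, f = 0.25, three groups, and two assumed settings that the article does not give (two measurements, within-person correlation 0.5). Then λ = f²·N·m/(1−ρ) = 0.0625 × 42 × 2/0.5 = 10.5 on 2 and 39 degrees of freedom, with power 0.803. Neither 42 nor 48 is disputed here.

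**2. Which allocation time fits which text.**

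| Text | Allocation before week 4 | Allocation after week 4 |
|---|---|---|
| Watch worn by MA, goal from baseline average (2.3.5, 2.4) | Fits | Fits only if all participants wear one in weeks 1–4 |
| Home participants have no draws in weeks 2–3 (Table 1, footnote c) | Fits | Does not fit: nobody yet knows who will be at home |
| Replacement before second baseline (2.2.1) with intention-to-treat (2.5) | In tension | Fits |

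The first two rows point to early allocation, the third to late allocation. As printed, no single time of randomisation fits all three rows without qualification.

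**3. How early it must be.** Home participants keep the week-1 draw, so the first difference in blood sampling is in week 2. The watch could be issued at the end of the week-1 visit. The text therefore requires the arm to be known after the week-1 visit and before week 4. It does not require it before the week-1 HADS.

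**4. Bias from a shifted week-4 HADS.** Let s be the difference between MA and a comparator arm in HADS at week 4 that is due to allocation. The documents give no value, so a range of 0.5 to 2 points is assumed.

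- Change from week 4: the observed MA change is (post − [baseline + s]), so the contrast moves by s.
- Change from the mean of weeks 1 and 4, with week 1 clean: the baseline moves by s/2, and so does the contrast.

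| Assumed s (points) | Bias, change from week 4 | Bias, mean of both baselines |
|---|---|---|
| 0.5 | 0.5 | 0.25 |
| 1 | 1 | 0.5 |
| 2 | 2 | 1 |

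The sign is open. If early walking lowers the MA score before week 4, MA appears to improve less afterwards and HIIT and CAT look better. If disappointment raises it, the reverse holds.

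**5. Replacement.** If allocation precedes the withdrawal window, a fraction w leaves before week 4 (assumed), and recruitment continues until 48 have passed it, the number randomised is 48/(1−w).

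| Assumed w | Randomised | Randomised beyond the 48 |
|---|---|---|
| 0% | 48.0 | 0 |
| 5% | 50.5 | 2.5 |
| 10% | 53.3 | 5.3 |
| 15% | 56.5 | 8.5 |

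With allocation after the second baseline, the last column is 0 at every w. For scale, with equal arms of 48/3 = 16, two replaced people would be 2/16 = 12.5% of an arm.

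**The case against.** The strongest reply is that randomisation timing is simply not reported. Figure 1, which may mark it, is not available here, and neither is the full protocol. That stands: early allocation is an inference from two procedures.

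The sentence in section 2.4 about providing a watch to each participant could be read as covering all arms. If so, the step-counter argument falls. The MA-only reading is more natural, because the sentence stands in the MA paragraph and section 2.3.5 speaks of this group. On either reading the blood schedule remains, although footnote c does not name an arm and its link to MA rests on MA being described as home-based.

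A reader might infer several stronger things that the documents do not support:

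- That both baseline HADS scores are post-allocation. Nothing excludes allocation just after the week-1 visit.
- That the replacement rule by itself breaches intention-to-treat. It does so only if the people replaced were already randomised. Section 2.2.1 also does not say that their data are discarded; a replacement can be recruited while the person who left stays in the analysis.
- That a 1-point shift costs a third of the planned effect. The 3 points in section 2.2.2 are the HIIT–CAT difference (6 − 3). The procedures in question separate MA from the other two arms, and the article gives no target for those contrasts.
- That the week-4 score anchors every estimate. Section 2.5 fits a mixed model across time points and does not say how the two baselines enter, so the bias could be halved, as in step 4.

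**Conclusion.** The point holds in conditional form. As printed, the step-counter text and the blood-sampling footnote imply that the arm is known before the second baseline. The week-4 HADS is then post-allocation and, unless the procedures are disguised in a way the article does not describe, open to the participant. This compromises the baseline-stability check and can bias the HIIT–MA and CAT–MA contrasts by 0.5–2 points (change from week 4) or 0.25–1 point (mean of both baselines, week 1 clean), for an assumed shift of 0.5–2 points. The cited procedures do not in themselves bias HIIT–CAT. Under the same early allocation, the replacement rule is at odds with intention-to-treat unless those replaced are retained in the analysis. If allocation in fact follows week 4, the replacement rule is harmless, and the step-counter and blood-sampling text is what needs correcting. The shift and the early withdrawal rate are assumptions. The conflict between the passages is not.

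**What to change.** 1. State when randomisation takes place relative to the week-1 and week-4 assessments and when participants learn their arm. Reconcile sections 2.3.5 and 2.4 on who wears the watch, and footnote c with that timing.
2. For participants not yet enrolled, allocate after the week-4 assessments are complete. Until then, keep step-counter wear (display hidden if possible) and the blood schedule identical for everyone. Replacement before the second baseline then concerns only people who have not been randomised.
3. For those already allocated earlier, keep every randomised participant in the intention-to-treat set and the participant flow, whether or not a replacement was recruited. Report how many were allocated under each procedure.

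Items 1 and 3 cost almost nothing. Item 2 needs step counters for all arms in weeks 1–4 and a new randomisation time in the data-capture system. Because enrolment is under way, it is also a mid-trial change that leaves participants allocated under two procedures, so it must be documented with its date.
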